### Objective

2.1

This study aims to assess the safety and efficacy of NHT in patients with FD.

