### Sample size calculation

2.5

We hypothesize that oral administration of NHT is more effective than that of placebo in relieving FD symptoms. As the first randomized clinical trial of NHT in patients with FD, we referred to a previous study with a modified design using the same primary outcome.^[20]^ The previous study showed 1.4 points of improvement (μ_c_ – μ_t__=_*δ*) in the TDS scores for FD patients after 4 weeks of treatment with a traditional Chinese herb. In this study, the ratio (λ) of the experimental group to the control group will be 1:1, and the sample size was calculated at the 5% significance level (α) and 80% power (1 – β). The formula used to estimate the sample size is as follows, assuming that the standard deviations (SD = σ) of two groups are different and applying the larger variance in common (
[figure not shown]
): 

Considering the dropout rate as 20%, we calculated the necessary sample size to be 116 participants (58 in each group).

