### Safety assessment

3.4

The following clinical laboratory parameters will be examined to assess the safety of NHT treatment at screening and week 4; white blood cell, red blood cell, hemoglobin, hematocrit, mean corpuscular volume, mean corpuscular hemoglobin, mean corpuscular hemoglobin concentration, mean platelet volume, platelet, aspartate aminotransferase, alanine aminotransferase, gamma-glutamyl transpeptidase, blood urea nitrogen, creatinine, total cholesterol, triglyceride, high density lipoprotein cholesterol, low density lipoprotein cholesterol, glucose, erythrocyte sedimentation rate, and urinalysis. At screening, these laboratory tests and electrocardiography will be executed to decide whether a subject is eligible to enroll before randomization. In addition, adverse events reporting during the study period will be analyzed to verify the safety of NHT in patients with FD.

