### Statistical analysis

3.9

The efficacy of NHT will be analyzed on the full analysis set and per-protocol analysis. The last observation carried forward method will replace missing data to assess the robustness in the results. The safety of NHT will be assessed for the participants who are randomly assigned and received the investigational drugs at least once. The outcomes will be handled by an independent statistician.

Statistical analysis will be performed by using the SPSS program, version 20.0 (IBM SPSS Statistics, New York). The data will be expressed as mean ± standard deviation or as numbers with proportions. The changes after taking the investigational drugs will be compared between the experimental group and the control group. A chi-square test or Fisher's exact test will be used for discrete variables, while independent two sample *t* test for continuous variables. Those that do not satisfy normality will be analyzed by the Mann–Whitney *U* test as a nonparametric statistical test. The analysis of variance will be used for subgroup analysis of the changes in each pattern identification. The assessment of long-term therapeutic effects in a certain period from allocation to close-out will be performed on the basis of repeated measures design. The statistical relationship between subjective components of each assessment and objective EGG parameters will be analyzed with regression analysis. For safety assessment, the frequency and severity of adverse events and the changes in laboratory measurements will be compared between two groups. *P*-values <.05 will be regarded as statistically significant.

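### The adverse-event analysis is meant to verify safety, but the only method stated is a between-group difference test, which can flag harm but cannot verify safety

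*Protocol article*

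**What the plan says.** Section 2.1 of the protocol article makes safety part of the single objective: "This study aims to assess the safety and efficacy of NHT in patients with FD". Section 3.4 then gives the purpose of the adverse-event analysis: "adverse events reporting during the study period will be analyzed to verify the safety of NHT in patients with FD".

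The method is in section 3.9: "For safety assessment, the frequency and severity of adverse events and the changes in laboratory measurements will be compared between two groups". The same section says "A chi-square test or Fisher's exact test will be used for discrete variables" and sets p<.05 as the significance threshold for all analyses. The safety set is everyone randomised who took at least one dose, so up to 58 per arm. Results are to be shown as means with standard deviations, or as counts with proportions.

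Section 2.5 sizes the trial on the TDS score only, from a 1.4-point difference at 5% significance and 80% power, with 20% dropout. It gives no expected adverse-event rate and no power for safety. The one explicit decision rule, in section 3.3.1, is for efficacy: a significant TDS difference at week 4 means that NHT is regarded as effective. Safety has no matching rule.

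**The concern.** The stated purpose and the stated method do not fit. A test of no difference has two outcomes. If it is significant, it points to harm (or benefit). If it is not, the data are compatible with no difference and also with every excess risk inside the confidence interval. Only an interval or bound says which excess risks have been excluded, and that is what a safety statement needs. The smaller the trial, the more easily a difference test gives a reassuring p-value.

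At stake is the wording of the safety conclusion. Section 4 presents this as the first randomised trial of the efficacy and safety of NHT. A report that adverse events did not differ significantly, set beside a declared aim of verifying safety, could carry more weight than 58 participants per arm can support.

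**Working it through.** **Inputs from the article.** 58 per arm; safety set of all dosed participants; chi-square or Fisher test; threshold .05 (taken as two-sided). Adverse-event rates are not given, so those below are assumptions shown over a range.

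**The plan's own figure.** 58 per arm agrees with 46 per arm inflated for dropout: 46 / (1 − 0.20) = 57.5, rounded up to 58. With a 1.4-point difference, 80% power and two-sided 5%, 46 per arm corresponds to an SD of about 2.37 to 2.40. The SD itself cannot be read (the formula is a figure not shown), so this is a consistency check only. No adverse-event rate enters the calculation.

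**Step 1: chance of missing a true increase.** For true rates p₀ (placebo) and p₁ (NHT), each possible pair of counts (a, b) has probability Bin(a; 58, p₁) × Bin(b; 58, p₀). Each pair was tested at two-sided .05, and the probabilities of the non-significant pairs were summed.

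| True rates, placebo → NHT | Missed, Fisher | Missed, uncorrected chi-square |
|---|---|---|
| Doubling, 5% → 10% | 92% | 83% |
| Doubling, 10% → 20% | 76% | 67% |
| Doubling, 15% → 30% | 59% | 50% |
| Doubling, 20% → 40% | 41% | 34% |
| Tripling, 5% → 15% | 69% | 55% |
| Tripling, 8% → 24% | 43% | 32% |
| Tripling, 10% → 30% | 28% | 20% |

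**Step 2: where missing becomes the likelier outcome.** Solving for the placebo rate at which the chance of significance is 50%:

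- doubling: 14.9% (chi-square), 17.4% (Fisher);
- tripling: 5.7% (chi-square), 7.1% (Fisher).

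Below these rates the increase is missed more often than not. Above them it is usually detected.

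**Step 3: what a non-significant result can hide.** Suppose 9/58 on NHT and 3/58 on placebo (15.5% v 5.2%).

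- Fisher p = .125; chi-square p = .067. Neither is significant.
- Risk difference = 6/58 = 10.3 points.
- Wilson limits are 8.4% to 26.9% for 9/58 and 1.8% to 14.1% for 3/58.
- Newcombe lower limit: 10.3 − √[(15.5 − 8.4)² + (14.1 − 5.2)²] = −1.1 points.
- Newcombe upper limit: 10.3 + √[(26.9 − 15.5)² + (5.2 − 1.8)²] = +22.3 points (limits computed from unrounded inputs).

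Even with equal observed rates, the interval is wide. The half-width 1.96 × √[2p(1 − p)/58] is 7.9 points at p = 5%, 10.9 at 10% and 14.6 at 20%.

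**Step 4: zero events of one type on NHT.** The exact upper bound for the true rate is 1 − 0.05^(1/58) = 5.0% (one-sided 95%), or 1 − 0.025^(1/58) = 6.2% (two-sided 95%).

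**The case against.** The strongest reply is that the article contains no rule of the kind criticised. A reader might infer that a non-significant comparison will be declared proof of safety, because section 3.4 speaks of verifying and section 3.3.1 uses significance as the verdict for efficacy. The article does not say so: section 2.1 speaks neutrally of assessing safety, and section 3.9 speaks only of comparing. This objection stands, and the point must not be put as an announced decision rule.

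A reader might also infer that any doubling or tripling would usually go unnoticed. The table does not support that. At 10% → 30% the test misses only 28% (Fisher) or 20% (chi-square), and at 20% → 40% only 41% or 34%. For a broad endpoint such as any adverse event, with a high background rate, the test performs better.

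Three further replies are fair.

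- Comparing adverse events without a margin is common in a trial sized for efficacy, and intervals may be specified in an analysis plan that is not shown. Their absence alone is therefore no error.
- Counts and proportions per arm will be reported, so readers could compute an interval themselves. Sections 2.10 and 3.6 also provide for recording and reporting adverse events.
- The sentence in section 4 about clinical practice guidelines follows from evidence of therapeutic effect. It does not say that the safety result will feed guidelines.

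What these replies leave standing is the mismatch in the published text: an aim of verifying safety, paired with a method that cannot deliver it.

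**Conclusion.** The point holds as a mismatch between the purpose in section 3.4 and the method in section 3.9. A difference test at .05, in a trial sized only on TDS, can show harm but cannot verify safety.

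How much this matters depends on background rates that the article does not give. It is serious for uncommon events (placebo rate below about 15–17% for a doubling, about 6–7% for a tripling) and milder for common ones. These figures assume the full safety set of 58 per arm and a two-sided test. They concern adverse-event incidence, not the laboratory comparison. The zero-event bound needs no assumed rate: 58 participants without an event of one type cannot exclude a true rate of 5.0% (one-sided 95%) or 6.2% (two-sided).

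This is a cheap and worthwhile correction to wording and reporting. It does not show that the trial would reach a false safety conclusion.

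**What to change.** In section 3.9:

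- For participants with any, drug-related and serious adverse events, report the NHT-minus-placebo risk difference with a 95% Newcombe or Miettinen–Nurminen interval.
- For event types with no cases on NHT, give the exact upper bound (5.0% one-sided or 6.2% two-sided at n = 58).
- State that p of .05 or more will not be taken as evidence of safety.

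In section 3.4, replace the verb *verify*, so that the aim is to describe the safety of NHT and estimate the excess risk.

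The cost is a few sentences and a few extra intervals, with no new data, visits or participants. The downside is a less favourable safety statement, because the intervals will be wide.

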## Discussion

4

FD is a common disease that results in personal distress and somatic symptoms, and causes high economic burden in the society.^[31,32]^ Currently, conventional drugs available for FD has been prescribed to patients, such as proton pump inhibitors (PPIs), histamine-2 receptor antagonists, and prokinetic agents.^[33]^ However, FD remains a challenging clinical problem because of its heterogeneous characteristics. Because of dissatisfaction with conventional therapies, herbal medicine have attracted FD patients’ attention as an alternative solution.^[34,35]^

Traditional herbal remedies have been generally used for the treatment of FD in traditional Korean medicine. Among them, NHT, a combined prescription of *Daehwajung-eum* and *Naeso-san* consisting of 19 herbs, has been frequently prescribed for dyspepsia for a long time. According to a previous study, it was found that some EGG findings in the postprandial phase were improved after 4-week administration of NHT on FD children with abdominal pain.^[19]^ In animal research on antral dilated rats to evaluate the effect of *Naeso-san*, gastric emptying and myoelectrical activity of gastric smooth muscle were measured. It was confirmed that *Naeso-san* activated gastric motility through the cholinergic pathway, increasing the significant postprandial dominant power and gastric emptying.^[36]^ In addition, *Daehwajung-eum* inhibited contractions on the isolated rat fundus-strip, induced by acetylcholine chloride and barium chloride.^[37]^ Based on these previous studies, NHT is expected to improve dysmotility-related FD symptoms by modulating gastric motility such as gastric adaptive relaxation. However, there is no randomized controlled trial assessing the safety and efficacy of NHT as a treatment of FD. Thus, we aim to obtain objective information about the efficacy of NHT to activate GI motility, and improve both FD symptoms and EGG findings simultaneously.^[38,39]^

EGG is a noninvasive method that uses surface-placed electrodes to evaluate GMA.^[40,41]^ Though there is a heterogeneity of association between dyspeptic symptoms and EGG recordings among previous studies,^[6,42,43]^ EGG is still useful and convenient method to detect abnormal gastric motility. In this study, participants will be subdivided into two subtypes; PDS, which includes overlap type, or EPS. EGG will be used to evaluate gastric motility in PDS group, and the results will be analyzed in comparison to other outcomes.

According to the guidelines for setting endpoint in the clinical trial for FD, it is recommended that 4 weeks of treatment is needed to demonstrate short-term effects of intervention, considering pharmacological effects of drugs and natural history of FD.^[44]^ In addition, 4-week period has been applied in most of clinical studies to investigate curative effects of medicine such as PPIs, prokinetics, and herbal medicine in the treatment of FD.^[33,45]^ Therefore, we set the ideal duration of administration to 4 weeks.

To evaluate the efficacy of NHT, the TDS score will be measured for the primary outcome, whereas OTE, SDS, FRQ, DQ, FD-QoL, and GMA will be studied as secondary outcomes. Comparison of subjective dyspeptic symptoms and objective assessments of gastric activity will improve reliability in research findings. The study will be published regardless of the results, in accordance with the consolidated standards of reporting trials (CONSORT) guidelines.

There are some limitations in this study. First, 4 weeks of follow-up period after treatment ends is relatively short. Second, more frequent implementation of EGG may be helpful for predicting treatment effects. Nevertheless, as the first randomized clinical trial to assess the efficacy and safety of NHT in patients with FD, the results of this study are expected to strengthen the evidence of therapeutic effects of NHT on FD. Thus, it can contribute to the development and implementation of clinical practice guidelines for effective treatment and management of FD, improving public health.
